##### Interim analysis

The final analysis for primary endpoint and secondary analysis will be performed after completion of study.

Interim analysis is planned 1 year and 2 years after study initiation. The purpose of interim analysis includes: (1) adjustment of sample size according to collected real data, (2) early termination of study if statistically significance reached comparing primary endpoint between BCM arm and control arm, (3) early termination of study if incidence rate of fluid management related adverse events is significantly high in the BCM arm.

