**Methods:**

This is a multicenter, prospective, randomized, controlled trial. More than 1300 participants from 16 clinical sites will be included in the study. The enrolment period will last 6 months, and minimum length of follow-up will be 36 months. MHD patients aged between 18 years and 80 years who have been on MHD for at least 3 months and meet eligibility criteria will be invited to participate in the study. Participants will be randomized to BIA arm or control arm in a 1:1 ratio. A portable whole body bioimpedance spectroscopy device (BCM—Fresenius Medical Care D GmbH) will be used for BIA measurement at baseline for both arms of the study. In the BIA arm, additional BCM measurements will be performed every 2 months. The primary intent-to-treat analysis will compare outcomes for a composite endpoint of death, acute myocardial infarction, stroke or incident peripheral arterial occlusive disease between groups. Secondary endpoints will include left ventricular wall thickness, blood pressure, medications, and incidence and length of hospitalization.

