## Methods

### Study design

This is an open label, multicenter, prospective, randomized controlled trial. The aim of the study is to assess if BIS guided fluid management can improve long term outcome in MHD patients. Body composition and hydration state will be assessed with a portable whole body bioimpedance spectroscopy device (BCM—Fresenius Medical Care D GmbH). The study will involve 16 clinical sites, enrolling more than 1300 participants. The enrolment period will last approximately 6 months, with a planned minimum 36 months follow-up period. Participants will be randomized to two arms, the control arm and BCM arm. Patients in both arms will receive BCM measurement, but results from the BCM measurement in the control group will be kept blinded to the investigators. Participants in control group will be followed up and their dry weights will be adjusted according to the dialysis center’s standard clinical practice. Clinicians managing participants in the BCM group, in addition to routine practice, will receive BCM measurement and dry weight will be adjusted according to BCM output data estimating overhydration and dry weight. All of baseline demographics, clinical data, laboratory data, regular BCM measurement, and ultrasonic cardiograph (UCG) data will be recorded on study case report forms (CRFs).

The flow chart of the study is shown in Figure
1.

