#### Sample size calculation

Literature search failed to identify a study of similar design to this one. In an observational study by Wizemann et al.
[1] of 269 MHD patients the patients were divided into hypervolemic group if their ECF was 15% higher than normal or normohydrated group if less than 15%. The patients were followed for an average 3.5 years. There was 41% death in the hypervolemic group, and 30% death in normohydrated group. Relative risk of death was 36.6% higher in hypervolemic group than in the other.

According to data from Beijing Hemodialysis Quality Control and Improvement Center, the annual mortality rate of Beijing MHD patients is around 10%, it is estimated that 3 year mortality to be 30%. It is also estimated that the rate of composite endpoint within 3 year period of time is 40%. We make an assumption that BCM guided fluid management will reduce the 3-year composite endpoint rate from 40% to 32% (20% relative risk reduction). To reach statistical significance with α < 0.05 and 1-β > 80%, the sample size required is 1128. Allowing for a 20% loss-to-follow-up, the total sample size planned is 1354.

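### The interim stopping rule is plain statistical significance with no adjusted level; if each of the three looks is tested at two-sided 0.05, overall type I error is about 11%

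*Protocol article*

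**What the plan says.** The Interim analysis section states the schedule: "Interim analysis is planned 1 year and 2 years after study initiation". It gives three purposes. The first is to adjust the sample size from accumulating data. The second is "early termination of study if statistically significance reached comparing primary endpoint between BCM arm and control arm". The third concerns an excess of fluid-related adverse events in the BCM arm. The same section adds a further test of the primary endpoint: "The final analysis for primary endpoint and secondary analysis will be performed after completion of study".

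The only significance level is under Sample size calculation: "To reach statistical significance with α < 0.05 and 1-β > 80%, the sample size required is 1128". The design effect there is to "reduce the 3-year composite endpoint rate from 40% to 32% (20% relative risk reduction". The Study design section sets the timeline: "The enrolment period will last approximately 6 months, with a planned minimum 36 months follow-up period".

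**The concern.** The primary endpoint can be tested three times, and the trigger for stopping is ordinary significance. The article attaches one meaning to that term, alpha below 0.05, and nothing in it reduces the level at any look. Repeated testing at an unreduced level inflates the chance of a false positive result.

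The extra errors would fall mostly at the interim looks, when events are few and an estimate that crosses the threshold tends to be exaggerated. A stop at year 1 or 2 would also forgo part of the planned 36 months of follow-up, in an open-label trial with death in the composite.

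The first interim purpose sits awkwardly with the timeline. With enrolment over at about 6 months, the looks come roughly 6 and 18 months after accrual has closed.

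**Working it through.** **1. Reproduce the plan's figure.** Inputs from Sample size calculation: 40% against 32%, alpha 0.05, power 80%. The 1:1 allocation is from the abstract. With pooled variance under the null and mean rate 0.36:

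n per arm = [1.960 × √(2 × 0.36 × 0.64) + 0.8416 × √(0.40 × 0.60 + 0.32 × 0.68)]² / 0.08² = 563.9, rounded up to 564. The total is **1128**, an exact match.

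The alternatives do not match: one-sided 890, two-sided with continuity correction 1178, two-sided unpooled 1124. So the stated size is a two-sided, single-look calculation at the full 0.05. The article does not state sidedness; it is inferred from this match.

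**2. Information at each look.** Assumptions: uniform accrual over A = 0.5 years, constant hazard giving 40% at 3 years in both arms (the null), no dropout, final analysis at 3.5 years.

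- λ = −ln(0.60)/3 = 0.1703 per year.
- Expected proportion with an event by calendar time t: F(t) = 1 − [exp(−λ(t − A)) − exp(−λt)]/(λA).
- F(1) = 0.1196, F(2) = 0.2575, F(3.5) = 0.4248.
- Information fractions: 0.1196/0.4248 = 0.282, 0.2575/0.4248 = 0.606, and 1.

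**3. Type I error with an unadjusted test at each look.** The three Z statistics are multivariate normal with correlations √(tᵢ/tⱼ): 0.68, 0.53 and 0.78. The probability that |Z| exceeds 1.96 at any look is:

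| Look | Added | Cumulative |
|---|---|---|
| Year 1 | 5.0% | 5.0% |
| Year 2 | 3.4% | 8.4% |
| Final | 2.7% | 11.1% |

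About three quarters of the false positives (8.4/11.1) arise at an interim look. In the direction of benefit only, the figure is 5.5% against 2.5%.

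**4. Sensitivity.** Equal thirds give 10.7%. Varying the 3-year event rate (36% or 40%), dropout (none or 20%) and the end of study (3.0 or 3.5 years) gives 10.6% to 11.1%. If each look were instead one-sided at 0.05, the overall one-sided error would be about 10.0% to 10.5%.

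**5. What a year-1 stop would need.** With 1128 patients, expected events are 1128 × 0.1196 ≈ 135. Reaching p < 0.05 for benefit needs a hazard ratio of about exp(−1.96 × 2/√135) = 0.71 or lower. The design effect corresponds to ln(0.68)/ln(0.60) = 0.755. With all 1354 planned patients and no loss, there would be about 162 events and the threshold would be 0.735, still more extreme than the design effect.

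**6. A boundary that holds 0.05.** Lan-DeMets O'Brien-Fleming-type spending with 0.025 per tail at 0.282/0.606/1 gives z of about 4.07, 2.65 and 1.98. The nominal two-sided p values are about 0.00005, 0.008 and just under 0.048. At N = 1128 the power falls from 80.0% to about 79.7%. A Pocock boundary at about 28%/60%/100% would test at about 0.021 each time and lower power to 72.7%.

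**The case against.** The strongest reply is that the article nowhere says each look is tested at 0.05. That level appears as a sample-size input and could be read as the overall level. Stopping once significance is reached could also describe a trial with a boundary. A condensed article commonly leaves boundaries to the analysis plan, which is not shown. Nor does the single-look 1128 rule a boundary out, since an O'Brien-Fleming type costs so little power that a designer might ignore it.

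This stands in part. A reader might infer that the protocol fixes 0.05 at every look and that 11% is the trial's actual error rate; the text does not go that far, so the figure is conditional. The point does not reduce to missing detail, however. The article states a trigger, that trigger is unqualified significance, and the only level it gives for significance is 0.05. An analysis plan that sets a boundary would be correcting the published rule.

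Two other stronger readings fail. The 11% counts both tails, so it is not the rate of false claims of benefit. And a reader might infer that the sample-size adjustment would use unblinded results. The article speaks only of data collected so far, which fits a pooled event rate equally well, and it gives the enrolment period as approximate. The timing conflict is real, but it is a question of feasibility and adds nothing to the 11%.

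**Conclusion.** The point holds in conditional form. As written, the rule permits stopping for ordinary significance at two interim looks before a final test, without saying that overall alpha is preserved. On the plain reading, with two-sided 0.05 each time, type I error is roughly double the intended level. The doubling does not depend on the accrual, dropout and timing assumptions within the range tried. What it does depend on is the level applied at each look, which the article leaves unsaid. The sample-size adjustment after enrolment has closed is a separate and lesser inconsistency between the Interim analysis and Study design sections.

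**What to change.** In the Interim analysis section, replace the significance trigger with this: the trial may stop for efficacy only if the primary comparison crosses a pre-specified group-sequential boundary that keeps the overall two-sided alpha at 0.05 across the year-1, year-2 and final analyses. Name the method. Lan-DeMets O'Brien-Fleming-type spending with 0.025 per tail is one suitable example, with the nominal levels in step 6 of the working recomputed at the event fractions actually observed. Any named procedure that controls the overall level would resolve the point. If the full analysis plan already sets a boundary, one sentence saying so is enough.

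Restate the first interim purpose as a pooled, arm-blind check of the event rate, with any shortfall met by longer follow-up. If an event target is wanted, it must be labelled as an assumption, because the article gives none. For example, a log-rank test at hazard ratio 0.755, two-sided 0.05 and 80% power needs 4 × (1.960 + 0.8416)²/(ln 0.755)² ≈ 398 events.

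The cost is a short amendment and, with the example boundary, less than 1 point of power at the stated 1128.

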#### Dry Weight Adjustment Strategy

All participants will be educated to reduce inter-dialysis weight gain to less than 5% body weight.

For participants in the control arm, dry weight will be adjusted according to the clinical site’s standard clinical practice.

For participants in the BCM arm, dry weight will be adjusted according to the BCM estimates of overhydration and normovolemic weight. During each dialysis session, participants’ dry weight will be increased or decreased toward BCM reported dry weight. The increment or decrement of dry weight will not be greater than 0.5 Kg within a single dialysis session. Thus, in this arm participants’ dry weights will be gradually adjusted to BCM reported value. If ultrafiltration is not tolerated because of hypovolemia based on symptoms and signs, such as muscle cramps, need for excessive saline, or symptomatic hypotension, adverse events will be recorded, and the actual dry weight will be adjusted by plus 0.5 Kg. If participants experience hypervolemic clinical episodes, such as hypertension related symptom, congestive heart failure, pulmonary edema, adverse events will also be recorded. If a patient experiences the same adverse effect of dry weight change for two consecutive visits, the patient will be removed from the study because of adverse event.

Dry weight adjustment flow chart in the BCM arm is shown in Figure
2.

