##### New diagnosis

Any newly emerged diagnosis is regarded as a clinical event and will be recorded; hypotension and related clinical episode, hypertension and related clinical episode, pulmonary infection, diarrhea, angina pectoris, myocardial infarction, ischemic and hemorrhagic stroke, peripheral arterial occlusive disease, newly diagnosed neoplasm.

All deaths will be recorded as to date of death and cause.

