### Dry weight adjustment in BCM arm

“Real dry weight” is unknown in BOCOMO study. BCM reported dry weight might by significantly higher or lower than the real dry weight, which will lead to hypervolemia related acute symptoms and hypovolemia related acute symptoms, respectively. They will also worsen patients’ long-term outcome. In these kinds of conditions, adverse events attributes to BCM arm will be recorded.

Another issue regarding dry weight adjustment in BCM arm is the amount of each dry weight increase or decrease. Large amount of dry weight change is not allowed because significant dry weight increase or decrease during one HD session will lead to dramatic blood volume increase or decrease during HD session and associated clinical manifestation.

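### The safety stopping rule rests on fluid-related adverse events that are listed and instructed for recording as such only in the BCM-arm text, and it does not say which record or comparator it uses.

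*Protocol article*

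**What the plan says.** **The rule.** Under Interim analysis, the protocol article states "Interim analysis is planned 1 year and 2 years after study initiation". The third listed purpose is to stop the study early if the "incidence rate of fluid management related adverse events is significantly high in the BCM arm". No comparator, test, threshold or data source is attached to it.

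**The BCM arm.** The Dry Weight Adjustment Strategy section has one paragraph on the BCM arm. It deals with intolerance of ultrafiltration, giving examples, "such as muscle cramps, need for excessive saline, or symptomatic hypotension, adverse events will be recorded", and then continues: "If participants experience hypervolemic clinical episodes, such as hypertension related symptom, congestive heart failure, pulmonary edema, adverse events will also be recorded". The Discussion section headed Dry weight adjustment in BCM arm returns to the subject and says that "adverse events attributes to BCM arm will be recorded".

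**The control arm.** The Dry Weight Adjustment Strategy section gives control patients one sentence, on adjusting dry weight by the site's usual practice. It contains no instruction on adverse events.

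**Both arms.** The New diagnosis section says "Any newly emerged diagnosis is regarded as a clinical event and will be recorded", and its list includes hypotension and hypertension episodes. Table 1 logs new clinical events throughout the study, including hospitalizations and dry weight adjustments. It also schedules a physical examination every 2 months (weight, blood pressure, heart rate, edema, pulmonary rales, before and after dialysis). None of this is limited to one arm.

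The Study design section describes the trial as open label.

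**The concern.** A stopping rule based on harm needs the harm to be ascertained in the same way in both arms. Here the event list, and the instruction to call these events adverse events, appear only in BCM-arm text. In the control arm the same morbidity is picked up through a log of clinical events and new diagnoses. Staff know the allocation, so nothing masks the difference in instructions.

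If rule (3) is applied as a comparison between arms, some of any excess in the BCM arm could reflect how events were recorded and not how often they happened. The trial could then be stopped on an artefact. An analysis plan written later could not repair this, because cramps or saline use that were never recorded in control patients cannot be recovered.

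**Working it through.** **Step 1: set the records side by side.**

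| Event in the BCM-arm paragraph | Named in a record that covers both arms? |
|---|---|
| Muscle cramps | No |
| Need for excessive saline | No |
| Symptomatic hypotension | Yes, as a hypotension episode under New diagnosis |
| Hypertension-related symptoms | Yes, as a hypertension episode under New diagnosis |
| Heart failure, pulmonary edema | Not by name. A new case is a new diagnosis; signs may appear at the 2-monthly examination; an admission is logged |

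Two differences remain. Cramps and saline need are named only for the BCM arm. The New diagnosis log is worded for something newly emerged, so it does not clearly count a second or third episode. The label also differs: rule (3) counts fluid-management adverse events, whereas control episodes are logged as clinical events.

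**Step 2: inputs for an illustration of size.** The document gives no figure for this rule, so there is none to reproduce.
- From the document: planned total 1354 with 1:1 allocation, so 1354 / 2 = 677 per arm.
- Assumed: the same true patient-level incidence p in both arms; full capture in the BCM arm; a fraction c of affected patients captured in the control arm; one look with a two-sided 0.05 test, counting only results in the direction of a higher BCM rate.

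**Step 3: formula.** Observed rates are p1 = p (BCM) and p2 = c × p (control), with mean m = (p1 + p2) / 2.
- SE0 = √(2m(1 − m) / n)
- SE1 = √([p1(1 − p1) + p2(1 − p2)] / n)
- P(BCM significantly higher) = 1 − Φ((1.96 × SE0 − (p1 − p2)) / SE1)

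**Step 4: worked case.** Take p = 20%, c = 80%, so 20% against 16% and m = 0.18.
- SE0 = √(2 × 0.18 × 0.82 / 677) = 0.02088
- SE1 = √((0.1600 + 0.1344) / 677) = 0.02085
- (1.96 × 0.02088 − 0.04) / 0.02085 = 0.044, so P = 0.48

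**Step 5: range, n = 677 per arm.**

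| True incidence | c = 100% | c = 90% | c = 80% |
|---|---|---|---|
| 5% | 2.5% | 6% | 14% |
| 10% | 2.5% | 9% | 25% |
| 20% | 2.5% | 15% | 48% |

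With 564 per arm (half of the 1128 required before the allowance for loss), the values at 10% incidence are 8% and 22%, and at 20% they are 14% and 42%. Two looks are planned, and testing twice would raise the overall chance. With equal capture the probability stays at 2.5% per look whatever the true incidence.

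**The case against.** Several points on the other side have force.

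- **Control events are recorded.** A reader might infer that fluid-related events are captured only in the BCM arm. The document does not support that: the New diagnosis section, the Hospitalization section and Table 1 cover both arms, and cramps might be logged as part of a hypotension episode. What stands is that the list and the adverse-event instruction are one-sided.
- **This is a condensed article.** The adverse-event wording sits in a dose-adjustment-style algorithm for dry weight, and the Discussion sentence comes under a BCM-arm heading, so mention of that arm alone is natural. The case report forms are not shown and may be symmetrical. This lowers confidence. It does not dispose of the point, because the article makes a trial-ending rule depend on events that it instructs sites to record as adverse events in one arm.
- **No comparator is named.** If rule (3) looks at the BCM arm alone, under-recording in controls cannot cause a false stop. That is correct, but then the phrase about being significantly high has no reference. Either reading needs a clarification.
- **The illustration works on patients, not episodes.** A patient with repeat episodes counts if any one is logged. With independent 70% capture per episode, two episodes give 1 − 0.3² = 91% and three give 1 − 0.3³ = 97%. Patient-level loss can therefore be much smaller than episode-level loss, and for that reason the illustration is kept to patient-level capture of 80% and above.
- **Harm beyond the interim looks.** A reader might infer that a final safety comparison would carry the same bias. The document states none: adverse events are in neither the primary nor the secondary endpoint list. Nor does it say that BCM-arm events are counted at every session.

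**Conclusion.** The point holds in a limited form. The events behind rule (3) are listed and instructed for recording as adverse events only for the BCM arm. Control episodes come through a general log and 2-monthly examinations that omit cramps and saline need and leave repeats unclear. The rule does not say which record or comparator applies. In an open-label trial, a between-arm comparison made on that basis could show an excess due to recording alone.

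The asymmetry is in the text; its size is not. Under the assumptions in the working (677 per arm, equal true patient-level incidence of 10% to 20%, control capture of 90% to 80%, one look), the chance of a false finding that the BCM arm is higher is about 9% to 48%, where 2.5% is intended. These figures show how sensitive the rule is. They do not predict what this trial would see. The primary sample size is not affected. The change should be made because it is cheap and the lost data could not be recovered later.

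**What to change.** Record the event list from the Dry Weight Adjustment Strategy section in both arms, on the same form, at the existing 2-monthly visits, covering events since the last visit and their number, whether or not dry weight was being changed. State rule (3) as a between-arm comparison of these commonly recorded events per patient-year, and word the Discussion sentence to match. If the case report forms already do this, a sentence in each place is enough.

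**Cost.** One extra form section for about 677 control patients at visits they already attend: 36 / 2 = 18 visits each over the minimum follow-up, or 677 × 18 = 12,186 form sections. No visit, procedure or change in sample size is needed. Recording at every dialysis session would not be cheap: at 2.5 sessions a week for 156 weeks it would mean 677 × 2.5 × 156, or about 264,000 records.

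**What remains.** Two-month recall will miss some minor episodes, but under the same form in both arms. Because the trial is open label, a shared form reduces differences in reporting and cannot rule them out.

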## Discussions

### Strengths

Previous results regarding the benefit of strict fluid control are conflicting due to small sample sizes and unstable dry weight estimating methods. To our knowledge this is the first large-scale, multicentre, prospective, randomized controlled trial to assess whether BIS-guided volume management improves outcomes of MHD patients. The endpoints of the BOCOMO study are of utmost importance to health care providers.

